## Abstract

**Background:**

Low-load, high-repetitive single-limb resistance training may increase limb muscle function and functional exercise capacity in patients with chronic obstructive pulmonary disease (COPD) while minimizing the occurrence of limiting exertional symptoms. Whether high-repetitive single-limb resistance training would perform better than high-repetitive two-limb resistance training is unknown. In addition, the mechanisms underlying possible benefits of high-repetitive resistance training has not been investigated. The aims of this study are to compare single versus two-limb high-repetitive resistance training in patients with COPD and to investigate mechanisms of action of these training modalities.

**Methods/Design:**

This trial is a prospective, assessor-blind, randomized controlled trial. The participants are patients with stable severe to very severe COPD who are older than 40 years of age and healthy controls. The intervention is single-limb, high-repetitive, resistance training with elastic bands, three times/week for 8 weeks.

The control is two-limb high-repetitive resistance training with elastic bands, three times/week for 8 weeks.

The primary outcomes is change in the 6-min walking distance after 8 weeks of single-limb or two-limb high-repetitive resistance training.

The secondary outcomes are changes in limb muscle strength and endurance capacity, key protein involved in quadriceps anabolic/catabolic signalization, fiber-type distribution and capillarization, subjective dyspnea and muscle fatigue, muscle oxygenation, cardiorespiratory demand and health-related quality-of-life after 8 weeks of single-limb or two-limb high-repetitive resistance training.

The acute effects of single-limb versus two-limb high-repetitive resistance training on contractile fatigue, exercise stimulus (the product of number of repetition and load), subjective dyspnea and muscle fatigue, muscle oxygenation, and cardiorespiratory demand during upper and lower limb exercises will also be investigated in patients with COPD and healthy controls.

Randomization will be performed using a random number generator by a person independent of the recruitment process, using 1:1 allocation to the intervention and the control group using random block sizes.

Blinding: All outcome assessors will be blinded to group assignment.

**Discussion:**

The results of this project will provide important information to help developing and implementing customized exercise training programs for patients with COPD.

**Trial registration:**

ClinicalTrials.gov Identifier NCT02283580 Registration date: 4 November 2014. First participant randomized: 10 November 2014.

**Electronic supplementary material:**

The online version of this article (doi:10.1186/s13063-015-0698-x) contains supplementary material, which is available to authorized users.

## Background

The key disabling features in chronic obstructive pulmonary disease (COPD) include exercise intolerance, dyspnea and leg fatigue [1-3]. Increased dyspnea during physical activity is also a major reason for patients seeking medical care and is associated with lower quality of life [4]. Limb muscle dysfunction is another frequent manifestation of COPD. Decreased limb muscle strength and endurance have been documented in this disease [5,6]. Since limb muscle dysfunction in COPD is strongly associated with exercise intolerance, improving muscle function is of upmost importance. Limb muscle weakness is considered as a significant determinant of reduced exercise capacity in COPD [6] and is present in all stages of the disease [7]. As a consequence, most previous studies on resistance training in patients with COPD primarily focus on increasing muscle strength, typically using high loads and low number of repetitions [6,8]. However, the benefits of this resistance training strategy on functional capacity (for example, walking) are small in this group of patients [8]. Since quadriceps endurance is a determinant of physical activity level [5] and may be reduced to a larger extent than quadriceps strength [9,5], the possibility of improving limb muscle endurance is of interest. To achieve this goal, high-repetition resistance exercises is recommended [10]. Furthermore, regardless the type of exercise performed, achieving an optimal exercise stimulus for involved muscles could be challenging in patients with COPD because ventilatory limitation and dyspnea may occur prior to contracting muscles being maximally stressed [11,12]. This is of importance because the degree of exercise stimulus is central to optimize benefits from the exercise training performed.

Partitioning the exercising muscle mass (that is, exercising using a single limb at a time) is a novel strategy used to reduce the extent to which the ventilatory limitation hinders the ability to reach sufficient exercise stimulus and to optimize the effects of the exercise training in patients with COPD [13]. A randomized controlled study using the concept of partitioning the exercising muscle mass performed as high-repetitive single-limb resistance training have recently been conducted by our group [14]. All resistance exercises within this study were executed with a single limb at a time in order to minimize to load on the ventilatory system to maximize the muscle-specific exercise stimulus [15,14]. It was found that 8 weeks of high-repetitive single-limb resistance training can improve walking capacity and muscle function while avoiding the occurrence of limiting exertional symptoms in patients with moderate to severe COPD [14]. However, since there was no active comparator, we do not know whether the single-limb execution of the resistance exercises would be more beneficial than when involving larger amount of muscle mass [16,17,14]. It could be anticipated that partitioning the exercising muscle mass during high-repetitive resistance training would allow the patients to maintain a high number of repetitions while being able to use higher loads or higher local training intensities than if a larger amount of muscle mass would be involved (for example, exercising with both legs or both arms simultaneously).

Another limitation of our study on high-repetitive single-limb resistance training is that potential structural and muscle adaptations could not be confirmed as the mechanisms underlying the improvements were not assessed [14]. The impact of high-repetitive resistance training on muscle fatigue was also not explored. This is potentially important considering that unpublished data from our laboratory indicate that high-repetitive single-leg exercise may induce muscle fatigue in the absence of muscle deoxygenation, considering that larger training effects have been shown in patients with COPD who develop quadriceps contractile fatigue during exercise training [18].

Lastly, the majority of patients included in this previous research had moderate airflow limitation, whereas high-repetitive single-limb resistance training would appear particularly suited for patients with advanced ventilator limitation. Thus, the overall aim of the current project is to investigate the muscular and functional effects of high-repetitive resistance training, in patients with severe to very severe COPD and to better understand the mechanisms of action of this training modality.

## Methods/Design

The study is a prospective, assessor-blind, block randomized, controlled, parallel-group trial constructed in accordance to the consolidate standards of reporting trials guidelines [19,20] (Figure 1). The study contains a chronic and an acute phase. In the chronic phase, the benefits of 8 weeks of single-limb and two-limb high-repetitive resistance training will be compared in patients with severe and very severe COPD. The acute phase will be used to investigate, at baseline, the acute physiological effects of single-limb and two-limb high-repetitive resistance training in patients with COPD and also in healthy controls. An overview of the two phases including a description of the testing procedure can be seen in Table 1.

**Figure 1 Fig1:**
[figure not shown]
Consolidate standards of reporting trials (CONSORT) flow diagram of trial design.

**Table 1 Tab1:** **Acute and chronic phase description**

**Acute phase**			**Chronic Phase**		
**Patients with COPD & Healthy controls**			**Patients with COPD**		
Visit 1	Visit 2 and 3*	R	Training	Visit 4	Visit 5 and 6
		A			
● Anthropometrics	● Muscle biopsy or 6MWT	N	High-repetitive single limb elastic band resistance training	● Anthropometrics	● Muscle biopsy (one visit)
● Voorips questionnaire		D		● Voorips questionnaire	High-repetitive single limb or two limb elastic band exercises
● CAT questionnaire †	High-repetitive single limb or two limb elastic band exercises	O		● CAT questionnaire	
				● Isokinetic measurements	
● Pulmonary function		M		● UULEX	● Muscle oxygenation
● Isokinetic measurements		I		● 6MWT	● Cardiorespiratory response
● UULEX †	● Muscle oxygenation				● Exertional symptoms
● 6MWT †	● Cardiorespiratory response	Z			● Muscle fatigability
● 25 RM testing	● Exertional symptoms	A			● Exercise stimulus
	● Muscle fatigability	T	High-repetitive two limb elastic band resistance training		
	● Exercise stimulus	I			
		O			
		N			
**Baseline measurements**			**8 weeks training**	**Post assessment**	

*Visit order is randomized. All visits are sepearated by at least 48 h.

†Only performed by patients with COPD.

6MWT, 6-minute walk test; CAT, COPD Assessment Test; COPD, chronic obstructive pulmonary disease; RM, repetition maximum, UULEX, unsupported upper limb exercise test.

### Objectives

#### Primary outcome

The primary outcome is change in the 6-min walking distance after 8 weeks of single-limb versus two-limb high-repetitive resistance training.

#### Secondary outcomes

The secondary outcomes are changes in the following:quadriceps endurance capacity;key protein involved in quadriceps anabolic/catabolic signalization, fiber-type distribution, enzymatic activities and capillarization;dyspnea and muscle fatigue perception;quadriceps oxygenation;cardiorespiratory response; andhealth-related quality-of-life, after 8 weeks of single-limb versus two-limb high-repetitive resistance training.

Secondary outcomes will also include acute effects of single-limb versus two-limb high-repetitive resistance exercises on the following:quadriceps contractile fatigue,exercise stimulus,dyspnea and muscle fatigue perception,muscle oxygenation and cardiorespiratory demand, andlimb muscle function (maximal strength and endurance).

### Hypotheses

The following hypotheses are proposed:Single-limb high-repetitive resistance training will provide a larger gain in the 6-min walking distance than the two-limb high-repetitive resistance training in patients with severe to very severe (stage 3 to 4) COPD.Eight weeks of single limb high-repetitive resistance training will be associated with larger physiological (muscle endurance, fatigue and deoxygenation) and structural (muscle protein synthesis, fiber-type distribution and capillarization) adaptations to training, and lower cardiorespiratory demand, as well a greater increase in health-related quality-of-life in comparison to two-limb high-repetitive resistance training.Two-limb high-repetitive resistance training will lead to larger restraints on the ventilatory system and higher dyspnea scores and, to reduced muscle fatigue, deoxygenation and localized exercise stimulus in comparison to single-limb high-repetitive resistance training in patients with COPD. Healthy controls will be able to train both legs/arms simultaneously without central constraints and with no differences in muscle fatigue or exercise stimulus between the two high-repetitive regimens.

### Settings

The study will be performed at Institut Universitaire de cardiologie et de pneumologie de Québec, Québec, Canada. Recruitment and data collection will begin in November 2014.

### Sample size and eligibility criteria

A total of 30 patients will be included. This sample size was calculated with the premises that 13 patients in each group would be required to obtain sufficient power to detect a 34-m (±30) between-group difference in the 6-minute walk test (6MWT), α = 0.05, β = 0.20 (80% power), and a two-tailed test of significance, based on the previous study on high-repetitive resistance training in COPD [14]. We are aiming to detect at least a 30-m difference between the two groups since this value is considered to be clinically significant in this population [21]. Considering a 15% drop-out rate in this type of study, a total of 30 patients will be recruited. In addition, for the acute phase of this protocol, a sample size of 11 patients with COPD and 11 controls is required to detect a relevant mean difference of 11% (±9) in limb muscle contractile fatigue between single-limb and two-limb execution of the exercises performed in the acute phase of this protocol for an α = 0.05, β = 0.20 (80% power), and a two-tailed test of significance based on a study by Rossman *et al*. comparing single-leg to two-leg knee extension in healthy adults [22].

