### Description of intervention and control groups

Patients with COPD will be randomized to either single or two-limb high-repetitive resistance training. Identical high-repetitive resistance exercise regimen will be used for both interventions, with one exception; the intervention group will perform the exercise regimen using a single limb at a time while the control group will, depending on exercise, perform the training using either both arms or both legs. A total of three sets will be performed for each limb. Training time will be shorter for the two-limb high-repetitive training group in comparison to the single-limb training group. To minimize any confounding effects of different amount of time spent with research staff, the control group will perform a light intensity balance exercise that will compensate for the difference in training time between the two interventions.

Both interventions will be provided on the basis of three sessions per week for 8 weeks. They will be performed under direct supervision, individually or in small groups of 2 to 4 participants. The care provider supervising the training will receive standardized education before the start of intervention consisting of written, oral and visual instructions on how to perform and instruct the exercises used in both high-repetitive protocols.

Before the actual training, there will be a 5-minute warm-up period on a stationary cross-trainer, focusing on muscle groups that will be trained during various exercises, including the latissimus row (m. latissimus dorsi), chest press (m. pectoralis major and m. deltoid anterior), knee extension (m. quadriceps), shoulder flexion (m. deltoid anterior), leg curl (m. hamstrings), elbow flexion (m. biceps brachii) and plantar flexion (mm. triceps surae). All exercises will be performed with elastic bands (Thera-Bands, The Hygenic Corporation [name]) with the exception of plantar flexion that will be executed using a weight-machine (Sport Art Fitness, Woodinville, WA, USA). Extended description of the exercise programs for the single-limb and the two-limb group including detailed including illustrations of start and end positions as well as execution of exercise movement is explained more in detail in the additional files [see Additional file 1 and 2].

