### Randomization and blinding

To prevent foreknowledge of treatment assignment and to keep the allocation sequence concealed from the participants and the researchers, group allocation will be done after the completion of baseline and inclusion tests by an individual independent of the recruitment process using a randomly permuted blocks design with a computer random number generator. Randomization will be performed with a 1:1 allocation to the intervention or control group. The allocation sequence will be kept in an opaque, sealed and stapled envelope and will be kept concealed until end of outcome assessment. The envelope will be made impermeable to intense light by using aluminum foil inside and sealed using tamper-proof labels. Furthermore, the participants will be given repeated instructions not to reveal their group allocation to the outcome assessors. In case of failure in keeping the outcome assessor blinded (that is, a patient reveals his/her group allocation), a second trained outcome assessor will be available.

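### The sample size gives 80% power at 34 m, but the protocol's stated target is 30 m, where power is about 69–72%; the 34 m comes from a study without an active comparator

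*Protocol article*

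**What the plan says.** All the sample size figures for the chronic phase stand in one paragraph of the protocol article, under Sample size and eligibility criteria. The calculation is that "13 patients in each group would be required to obtain sufficient power to detect a 34-m (±30) between-group difference" in the 6-minute walk test. Its remaining settings and its source are given as "α = 0.05, β = 0.20 (80% power), and a two-tailed test of significance, based on the previous study on high-repetitive resistance training in COPD". The next sentence gives the aim: "We are aiming to detect at least a 30-m difference between the two groups since this value is considered to be clinically significant". The total follows: "Considering a 15% drop-out rate in this type of study, a total of 30 patients will be recruited". Neither a sample size nor a power is given for 30 m.

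Two other sections bear on the source of the 34 m. The Background says of the earlier study that "since there was no active comparator, we do not know whether the single-limb execution of the resistance exercises would be more beneficial" than exercising a larger muscle mass. In the present trial the control is an active programme. Under Description of intervention and control groups: "Identical high-repetitive resistance exercise regimen will be used for both interventions, with one exception", namely one limb at a time against both limbs together.

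**The concern.** Two adjacent sentences name two different differences. The one that was powered (34 m) is larger than the one presented as the aim and as the clinically significant value (30 m). Because 34 m is easier to detect, the stated 80% does not apply at 30 m. A reader who takes the paragraph as a whole will believe the trial has a 20% chance of missing a true 30-m advantage of single-limb training on the primary outcome. The actual chance is nearer 30%. If the result is not significant, that reader would give it more weight against a clinically relevant benefit than the design supports.

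The second issue is where the 34 m comes from. A planning value from a study without an active comparator does not estimate the contrast between two active training modes. The article itself says the earlier study could not answer that question, yet uses it to size the trial that will.

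**Working it through.** **Inputs.** Difference 34 m and spread ±30, two-sided α = 0.05, 80% power, 13 per group, 30 in total and 15% drop-out, all from Sample size and eligibility criteria. Equal allocation is from Randomization and blinding ("Randomization will be performed with a 1:1 allocation to the intervention or control group"). The ±30 is not labelled. I read it as the common SD of the change in walking distance, because that reading reproduces the stated 13.

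**Step 1: reproduce the plan's figure.** Normal approximation, per group:

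n = 2 × (1.960 + 0.842)² × (SD / difference)²

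- 34 m: 2 × 7.85 × (30/34)² = 12.2, so 13. This matches the article.
- The exact noncentral t calculation gives 13.25, so 14, which is one patient per group away.

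**Step 2: power with 13 per group.** The standard error is 30 × √(2/13) = 11.77 m. Under the normal approximation, power = Φ(difference / SE − 1.96).

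- 34 m: Φ(2.89 − 1.96) = 82%; noncentral t, 79%.
- 30 m: Φ(2.55 − 1.96) = 72%; noncentral t, 69%.

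**Step 3: best case, all 30 complete (15 per group).** The standard error is 30 × √(2/15) = 10.95 m.

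- 30 m: Φ(2.74 − 1.96) = 78%; noncentral t, 75%.

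**Step 4: what 80% power at 30 m would take.**

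- 2 × 7.85 × (30/30)² = 15.7, so 16 per group; noncentral t, 16.7, so 17.
- Allowing for 15% drop-out: 32 / 0.85 = 37.6, so 38 recruited; or 34 / 0.85 = 40 recruited.

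**Step 5: smallest true difference detectable with 80% power.**

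| Evaluable per group | Normal | Noncentral t |
|---|---|---|
| 13 | 33.0 m | 34.4 m |
| 15 | 30.7 m | 31.8 m |

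**Step 6: how far the SD would have to fall.** Power depends only on difference / SD. With 13 per group, 80% power at 30 m therefore needs an SD of 30 × 30/33.0 = 27.3 m (normal) or 30 × 30/34.4 = 26.2 m (t), against the stated 30 m.

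**Step 7: source of the 34 m.** No arithmetic applies. The sample size paragraph bases the calculation on the earlier study, the Background says that study had no active comparator, and the intervention section describes a control that differs from the intervention only in using both limbs. No section explains why a value from the first setting should hold in the second.

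**The case against.** The strongest defence is that the article attaches 80% power to 34 m only and never claims it for 30 m. On this view the 30-m sentence merely explains why 34 m is worth detecting, or refers to an observed difference. There is something in this. With 13 per group and SD 30, an observed difference of about 2.064 × 11.77 = 24.3 m already reaches two-sided p < 0.05, so an observed 30 m would be significant. But the sentence presents 30 m as what the trial aims to detect, directly after a power statement, and significance of an observed 30 m is not 80% power against a true 30 m. The wording is loose rather than plainly false, and the mismatch remains.

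A second defence is that the mixed-model analysis planned under Statistics might be more precise than the simple comparison used for planning. It might, but the SD would have to fall to about 26–27 m, and nothing in the article says that it will.

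On the origin of the 34 m, a reader might infer that the plan assumes two-limb training adds nothing to walking distance, or that the true difference must be smaller than 34 m. The documents support neither. They do not say whether 34 m was a between-group contrast, a within-group gain or a rounded planning value. The Background adds that most of the earlier patients had moderate airflow limitation and that single-limb training should suit advanced disease particularly well, so the populations differ too. What stands is narrower: the source had no active comparator, and the transfer is not justified.

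It is also fair to say that no section announces that a non-significant result will be read as equal effect. The hypothesis is one of superiority. The risk of misreading comes from the power statement, not from a declared rule.

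**Conclusion.** The point holds as an inconsistency between the powered difference and the stated target. At the article's own 30-m target, power is about 69–72% with 13 evaluable per group and 75–78% with no drop-out at all. The type II error at 30 m is therefore about 28–31% with 13 per group, instead of 20%. In addition, the 34 m rests on a study without an active comparator, and its use here is unexplained. Both conclusions assume that ±30 is the SD of change and that the groups are equal in size.

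Two stronger readings should be resisted. The sample size arithmetic is not wrong: 13 per group follows from 34 m and 30 m, and power is at least about 80% for any true difference of 34 m or more. Nor is the drop-out allowance a real shortfall: 26 × 1.15 = 29.9 gives 30, and 26 / 0.85 = 30.6 is within one patient of it.

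**What to change.** Keep the planned number of patients and reword the paragraph under Sample size and eligibility criteria to say three things:

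1. With 13 evaluable per group and SD 30 m, power is about 80% for a true difference of 34 m or more and about 69–72% for the 30-m clinically significant difference.
2. The 34-m planning value is based on a study without an active comparator. Its relevance to single-limb against two-limb training is an assumption.
3. The primary result will be interpreted from the 95% confidence interval of the between-group difference, set against 30 m, so that a non-significant p-value is not taken as 80%-powered evidence against a 30-m benefit.

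This changes no procedure, allocation or recruitment target, so it is feasible although the trial was already recruiting when the article was submitted. The only cost is a less favourable stated power.

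### The 11 healthy controls are sized to detect a single- versus two-limb fatigue difference that the third hypothesis expects to be absent in them, and the planned t-tests alone cannot show that absence or its specificity to COPD

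*Protocol article*

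**What the plan says.** The protocol article, under Sample size and eligibility criteria, sets the acute-phase target at 11 people in each group, patients and controls alike. The effect on which this number rests is described as follows: "relevant mean difference of 11% (±9) in limb muscle contractile fatigue between single-limb and two-limb execution". The test conditions are given as "for an α = 0.05, β = 0.20 (80% power), and a two-tailed test of significance". The protocol bases this calculation on a cited study "comparing single-leg to two-leg knee extension in healthy adults".

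The third item under Hypotheses predicts less muscle fatigue with two-limb than with single-limb exercise in patients with COPD. When it compares the regimens in the healthy group, its prediction is this: "Healthy controls will be able to train both legs/arms simultaneously without central constraints and with no differences in muscle fatigue or exercise stimulus".

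Each participant performs both modes, on separate visits (Table 1; Limb muscle function). The Statistics section assigns Student t-tests to the comparison of single- and two-limb exercise. It gives no margin for concluding no difference and no comparison of the mode effect between patients and controls.

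**The concern.** The sample-size sentence and the third hypothesis point in different directions for the same people. The controls are sized to find a difference, with planning figures tied to healthy adults, while the hypothesis says healthy controls will not show one. The protocol does not explain how the two fit together.

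Two consequences follow for the analysis. First, if the hypothesis is right, the 80% power refers to an event that is not expected to occur in the controls. The planned t-test would then reject only at its 5% error rate, and failure to reject is not evidence of no difference. Second, the interest of having controls lies in whether the single-limb effect belongs to COPD. Finding significance in patients and none in controls does not answer that, because two separate tests can differ in outcome without the two effects differing.

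At stake is what the acute phase can conclude from its healthy group. The primary outcome, its sample size and its analysis are not affected.

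**Working it through.** **Inputs.** From the sample-size section: difference 11 points, ±9, two-sided α = 0.05, 80% power, 11 per group, 30 patients recruited in total. From Table 1 and Procedure: all patients do the acute visits before randomization, as their baseline. The text does not say whether ±9 is the SD within one mode or the SD of the paired difference. I assume an SD of the paired difference of 9, with a range of 6.4 to 12.7. The limits are 9/√2 ≈ 6.4 and 9 × √2 ≈ 12.7; the upper one is what a per-mode SD of 9 gives with zero correlation between modes.

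**1. The stated size.** With the two-independent-group formula, n = 2 × [9 × (1.96 + 0.84)/11]² = 10.5, rounded up to 11 per group. The figure reproduces, so there is no arithmetic error. (Each person does both modes, so a paired formula would also be natural. If 9 is the paired SD, 11 people have about 95% power for 11 points.)

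**2. What that power refers to in the controls.** It is the chance of a significant result if the true mode difference is 11 points. Under the third hypothesis the true difference is 0, and the chance of a significant result is 5% whatever the sample size.

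**3. Precision from 11 controls.** The 90% interval half-width is t(0.95, 10 df) × SD/√11 = 1.812 × SD/3.317.

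| SD of paired difference | 90% half-width (points) | Chance that the 90% interval lies within ±11 if the truth is 0 |
|---|---|---|
| 6.4 | ±3.5 | >99% |
| 9 | ±4.9 | about 97% |
| 12.7 | ±6.9 | about 70% |

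The last column was simulated. It uses ±11 because that is the only difference the protocol calls relevant. With an illustrative margin of half that size, ±5.5 points, the chance with 11 controls would be 24% at SD 9 and 3% at SD 12.7.

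**4. The contrast that bears on COPD specificity.** This is the single- minus two-limb difference in patients minus the same difference in controls, tested with a two-sample t-test. The assumed truth is 11 points in patients and 0 in controls. The standard error is SD × √(1/n₁ + 1/11). At SD 9 it is 3.17 with 30 patients (11/3.17 = 3.47 standard errors) and 3.84 with 11 patients (11/3.84 = 2.87).

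| SD of paired difference | Power, 30 patients v 11 controls | Power, 11 v 11 |
|---|---|---|
| 6.4 | 99.7% | 97% |
| 9 | 92% | 78% |
| 12.7 | 67% | 49% |

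**The case against.** The strongest reply is that sizing a group to detect a relevant difference is what makes a null result informative. That stands: if the truth is zero, 11 controls would exclude ±11 points in about 97% of trials at SD 9 and about 70% at SD 12.7. A reader might infer that the control sample is too small to be of use, and these figures do not support that. They do, however, concern the confidence interval. They help only if the interval is reported and judged against a stated difference, and the protocol states only the t-test.

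A reader might also infer that the planning source refutes the third hypothesis, since 11 controls would almost always show a difference of 11 points if it were there. The documents do not support this either. They say the calculation is based on the cited study, not which of the figures came from it. The source cannot be checked here. Its task is knee extension, whereas these participants do six elastic-band exercises, and the controls are aged 40 or over with physically active people excluded. The mismatch is unexplained; it is not a proven contradiction of fact.

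Finally, the hypothesis can be read as two separate within-group statements, which t-tests match, and a hypothesis is allowed to fail. That is fair, and the prediction need not be abandoned. But its two halves together say that the mode effect differs between patients and controls, and no planned test addresses that.

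**Conclusion.** The point holds as a mismatch between the sample-size statement and the third hypothesis, on a secondary objective. The 80% power quoted for the 11 controls is power for an effect the protocol expects them not to have, and a non-significant t-test would show neither no difference nor COPD specificity.

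The design itself can do better than the stated analysis. The existing participants give useful precision in controls and, at SD 9 with all 30 patients contributing, good power for the patient-control contrast. At SD 12.7 both are weaker. These results rest on the assumed SD of the paired difference, equal SDs in the two groups, an 11-point effect in patients, and complete acute-phase data. If only the calculated 11 patients contribute, the lower power column applies.

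**What to change.** 1. Reconcile the sample-size section with the third hypothesis: label the 11% (±9) as an assumption borrowed from healthy adults for the patients, say why it is thought to apply to them, and say whether ±9 is a per-mode SD or the SD of the paired difference.
2. Test the COPD-specific claim as the patient-versus-control difference in the single- minus two-limb effect (the group-by-mode contrast). Report the control mode difference with its confidence interval and do not rely on non-significance. If a conclusion of no difference is wanted, state beforehand the margin against which the interval will be read.
3. Replace the detection claim for controls with what the sample delivers at a stated SD: the interval half-width in 11 controls and the power of the contrast with the number of patients who actually do the acute visits.

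The cost is rewording in the sample-size, hypothesis and statistics sections and one further contrast on data already being collected. No participants or visits are added. The change should be made before the acute-phase data are analysed.
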